**Primary explanatory variables**							
	Program type	Programs supporting PrEP^b^ initiation or retention		Health jurisdiction surveys and legal extraction data		Intervention program implemented	
	Funding spent	Dollars in staffing and direct costs expended to conduct each program		Health jurisdiction surveys		Surrogate for program magnitude	

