To understand the impact of PrEP policies and programs (objective 2), we will leverage the legal coding and health jurisdiction program provision datasets described above to conduct quasi-experiments with outcomes of PrEP starts, PnR, and retention in care. PrEP programs have been adopted by local health authorities in the context of the disbursement of EHE funds as grants to applicants. Despite the lack of random assignment of jurisdictions to policies and programs, we propose a quasi-experimental design that allows us to have findings that reflect several of the characteristics of randomized studies, including temporality and controlling for time-invariant factors. Although quasi-experimental approaches are subject to some limitations inherent to nonrandomized designs such as challenges in controlling for time-varying characteristics, these designs minimize bias relative to other analysis approaches. Moreover, quasi-experimental approaches improve upon the external validity of randomized studies because the data stem from programs that have been enacted in practice. Because of the study design, results will be well positioned to inform real-world programs such as those that comprise EHE efforts. For quasi-experiments, we will conduct analyses using methods such as difference-in-differences (DID) that account for intervention and control jurisdiction trends before program implementation. Because interventions are implemented at different points in time, we will use the heterogeneous DID method proposed by Callaway and Sant’Anna [32] or a similar method to account for potential confounding from multiple implementation periods. Health jurisdictions implementing a program or policy will be the primary intervention unit, and controls will be jurisdictions not implementing a program. DID analyses will be accomplished with regressions that include a term for group (eg, telemedicine PrEP program or not), period (month), and group-by-period interactions that serve to estimate the effect of the intervention. Our approach provides a relatively large sample size for such analyses, with many of the 50 counties or local jurisdictions funded under the EHE program implementing programs under assessment, and other non-EHE jurisdictions also implementing some of the identified programs. Control jurisdictions will be counties or states in the United States that do not implement a particular program, using 9 years of monthly PrEP use data (2016-2024). Depending on characteristics of the intervention, such as statewide provision, we may restrict the control group to jurisdictions meeting certain criteria in order to improve the match between intervention and control groups. For instance, we might match counties by HIV prevalence or jurisdiction size.

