
Although we have conducted substantial outreach to health jurisdictions to optimize engagement, we anticipate that there will be some missing data from the health jurisdiction survey. It is likely not a valid approach to impute data on whether a program was implemented in a particular jurisdiction. Therefore, analyses will be conducted only among jurisdictions providing data. To explore the impact of the missingness, we will assess descriptive differences between missing and nonmissing jurisdictions for the outcome over time and for key sociodemographic variables. Our outcome assessment will include the determination of policy impacts on PnR, an equity metric. Additionally, we will identify potential inequities in PrEP use based on key geographic, socioeconomic, and demographic characteristics. This may be conducted empirically with interaction terms between the policies of interest and these characteristics. DID models assume that trends in the intervention and control groups are parallel before the intervention. This is a critical consideration because control jurisdictions might have additional interventions to the one under consideration. We will seek to assess the validity of this premise, using techniques such as visual assessments of event-study plots and the Granger causality test to determine whether the design is sufficient to meet the parallel trends assumption. If parallel trends assumptions are not met, we will consider alternative approaches such as multivariable matching, lagged dependent variable regression, and synthetic control models (adapted for multiple treated units). The synthetic control method uses a matching algorithm to create a weighted dataset for the control (nonintervention) group, assigning a weight to each element in the group to eliminate prior differences in critical covariates and the outcome. Another option is to use difference-in-difference-in-differences (DDD) to assess the additional change from a specific policy (eg, telemedicine) above and beyond the overall EHE program effect for funded EHE jurisdictions. The nature of the DID and DDD designs controls for confounders that do not vary over time. Therefore, to optimize model efficiency, we will not control for variables expected to remain constant over time (eg, area-level poverty), only adding time-variant covariates. To further ascertain the validity of the DID approach, we will conduct placebo tests for policies that our models have found to have statistically significant effects on PrEP use. These tests assign earlier implementation dates selected at random (eg, false) to treated units to observe if we continue to reject the null hypothesis under these “false” implementation dates. Statistically insignificant results from the placebo tests will increase confidence that the model outcomes are valid. Further, we will assess the sensitivity of our models to the implementation time period by conducting the Bacon-Goodman [33] decomposition and reporting any disproportionate influence of certain implementation periods. We will seek to conduct additional sensitivity analyses that explore whether funding levels determine the impact of programs, with the program intervention variable being related to prevention budget expended rather than whether the program was enacted. Analyses will be conducted in SAS 9.4, STATA 19, or similar software. Given that there are multiple policies, it will be critical to address challenges with multiple comparisons. To accomplish this, we will, where possible, seek unified model approaches that simultaneously test the effects of multiple programs.

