### Limitations

The aggregated medical claims dataset that provides PrEP use outcome data for all study aims contains a majority of claims in the United States but is subject to a number of limitations. First, it does not include prescriptions from closed health care systems, including the Veterans Affairs. Data must therefore be interpreted with caution for areas with high numbers of persons enrolled in closed health care systems, such as Kaiser Permanente users. Second, PrEP use in clinical trials and other informal channels may not be captured by the claims dataset. A limitation of the quasi-experimental approach is the lack of randomization to determine the effects of programs and policies, a limitation inherent to such assessments. We will minimize the impact of this limitation by using analytic designs that carefully adjust for secular trends and will also explore in our findings other considerations for establishing a causal relationship, including effect size, dose-response, and plausibility of the causal mechanism (eg, some programs might be anticipated to have a higher impact on care initiation than retention in care). Another limitation of the quasi-experimental approach is that the COVID-19 pandemic impacted PrEP use during the epidemic period [58-60]; this could influence the outcomes of analyses. To address this challenge, we will conduct a series of visual and quantitative sensitivity analyses for each program or policy that considers the pandemic period and its impact on results. There is a dependency in identifying programs with positive effects and modeling of these effects. We anticipate that some of the funds invested in EHE will have a quantifiable impact on PrEP use and care retention, but if we find no impact from any programs, we will conduct modeling informed by other data, such as those from clinical trials and observational studies. Another limitation is that funding for EHE programs could be discontinued, but based on our power calculations, we still will have sufficient data to perform the program and policy analyses, and evidence of success may become critical to encouraging funding reauthorization. Another potential challenge is the possibility of new medication approvals; we have discussed this with our aggregated data provider, and the contract will include all current and future PrEP medication data. Lastly, while the general structure of the algorithm may be applicable to other datasets, it may not be fully transferable due to potential variations in data structure, coding practices, and available variables across different data providers.

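### Replacing the program indicator with dollars means the funding analysis cannot separate having a program from spending more on it, if controls sit at zero dollars

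*Protocol article*

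**What the plan says.** All references are to the protocol article.

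- **Main analysis (Data Analyses, objective 2).** The difference-in-differences (DID) regressions use a yes/no group term, and "controls will be jurisdictions not implementing a program".
- **Funding analysis (same section).** The authors hope to add a check on the role of money in how well a program works. Its exposure coding is described as follows: "with the program intervention variable being related to prevention budget expended rather than whether the program was enacted".
- **Definition of funding (Table 1, primary explanatory variables).** Funding spent is "Dollars in staffing and direct costs expended to conduct each program", and its role is given as "Surrogate for program magnitude".
- **Causal reasoning (Limitations).** The authors will also explore "other considerations for establishing a causal relationship, including effect size, dose-response, and plausibility of the causal mechanism".

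The article does not say that the enactment term stays in the funding model or that the model is limited to implementers. It also does not say how controls are coded on the dollar variable.

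**The concern.** The question is whether, among jurisdictions that ran a program, those that spent more gained more. The stated coding puts dollars in place of enactment. If controls are at zero dollars, the fitted line is anchored at the controls and pulled up by every implementer, large or small spender. A program that gives each implementer the same gain, whatever it spent, still produces an upward slope.

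Funding is one of two primary explanatory variables, and the project's purpose is to guide future prevention investment. A slope that largely restates the yes/no effect could be read as evidence that further dollars buy further PrEP starts. If it were also used for the dose-response consideration, it would add little beyond the main estimate while appearing to corroborate it.

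**Working it through.** **Inputs from the Power Calculation section.** These are a minimum of 6 implementing and 238 control counties, 90% power and significance 0.05 (taken as two-sided; the article does not say). The article gives no figure for the funding analysis, so there is none to reproduce.

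**Assumptions, not in the article.**
- Controls have zero program dollars.
- The program effect τ is the same in every implementer, so the true slope on dollars is zero.
- Dollars among implementers are lognormal with coefficient of variation (CV) 0.25 to 1.5.
- Larger programs have 25 or 50 implementers among the same 244 counties.
- The model is a collapsed pre/post DID on county change scores, fitted by ordinary least squares.
- Noise is set so that the yes/no test has about 90% power.

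**Step 1: what the dollars-only slope estimates.** With many controls the intercept is close to the control mean. Then

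slope ≈ Σ(d·τ)/Σd² = τ·mean(d)/mean(d²) = (τ/mean(d)) × 1/(1+CV²).

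Per average budget the slope is τ/(1+CV²), although the true value is zero. With τ set at the plan's detectable difference of 2.4 starts per 100,000 and CV 0.5, this is 2.4/1.25 = 1.92 spurious extra starts per 100,000 for each additional mean budget.

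**Step 2: how often it is significant.** The yes/no test has noncentrality 1.960 + 1.282 = 3.24. Replacing the indicator by dollars multiplies it by 1/√(1+CV²) when implementers are a small share:

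- CV 0.3: 3.24/1.044 = 3.10, rejection about 87%
- CV 0.5: 3.24/1.118 = 2.90, about 83%
- CV 1.0: 3.24/1.414 = 2.29, about 63%

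**Step 3: simulation, 4,000 runs per cell.** Rejection rate of the dollars-only slope when the true slope is zero:

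| Implementers vs controls | CV 0.25 | CV 0.5 | CV 1.0 | CV 1.5 |
|---|---|---|---|---|
| 6 vs 238 | 89% | 84% | 75% | 68% |
| 25 vs 219 | 88% | 82% | 65% | 54% |
| 50 vs 194 | 87% | 81% | 61% | 45% |

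The mean slope per average budget was 0.37 to 0.97 of τ.

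**Step 4: no program effect.** With τ = 0 and CV 0.5, the dollars-only slope rejects in 4% to 5% of runs. The artefact therefore needs a real program effect.

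**Step 5: with the indicator kept.** The dollar term rejects in 4.5% to 5.6% of runs in every cell. Fitting dollars among implementers only gives 4.7% to 5.3%. Both are close to the nominal 5%.

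**Step 6: what the repaired term can detect.** Now let the effect be fully proportional to dollars, with mean τ. At 6 vs 238 the added dollar term has power of about 14%, 29% and 54% at CV 0.3, 0.5 and 1.0. The implementers-only fit has about 10%, 20% and 42%. With 50 implementers the added term has a little under 20% at CV 0.3 and a little over 40% at CV 0.5.

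**The case against.** The strongest reply is that the article does not fully fix the criticised model. The analysis is plural, tentative and exploratory, and the variable is only said to be related to budget expended. Spending tiers, with a low-versus-high contrast among implementers, would fit that wording and avoid the problem. Zero-dollar controls are inferred by joining Table 1 to the control definition. If prevention budget means a jurisdiction's whole prevention spending, controls are not at zero. The simulated estimator is also simpler than the planned monthly, staggered-adoption analysis, so the percentages are illustrative.

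These points stand as limits and make the concern conditional. They do not remove it. The article says dollars are used rather than enactment, which describes replacement, and Table 1 defines the dollars per program. An analyst who follows that wording gets a slope that cannot answer the stated question.

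Three stronger readings are tempting, and the article does not support them:

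- **Zero-dollar controls alone create a dose-response.** They do not. Without a program effect the rejection rate is about 5%.
- **A program whose effect is flat in dollars will always be reported as funding-driven.** The rate was 45% to 89% under the stated assumptions, and it drops below half in one cell of the table.
- **The authors have committed to citing this slope as causal evidence.** Limitations lists dose-response among general considerations and does not tie it to the funding model.

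**Conclusion.** The concern holds in conditional form. If the dollar variable is program-specific and replaces the enactment term, its slope confounds having the program with spending more on it. For an effective program whose effect is unrelated to dollars, the slope will often be wrongly taken as a funding effect. The article gives no CV of dollars, and the percentages also rest on a wholly flat effect and the collapsed model. The direction of the error needs only zero-dollar controls and a real program effect.

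The yes/no DID estimate is untouched, so this is a change that should be made to a secondary analysis and not a flaw in the main result.

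**What to change.** In Data Analyses, objective 2:

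1. State how controls are coded on the dollar variable.
2. Keep the enactment indicator and add dollars centred at the implementers' mean, set to zero for controls. Alternatively, fit the gradient among implementers only.
3. Draw any conclusion about funding level only from that term.
4. Report its confidence interval. State that with few implementers, for example the minimum of 6, the term is imprecise, so a null result does not show that funding is irrelevant.

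In Limitations, if the funding analysis is used for the dose-response consideration, base it on the same term.

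The cost is one model term and a few sentences. The price in precision is real, as the power figures above show, but it reflects how little a handful of implementers can say about funding level.

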## Methods

### Research Setting and Population

The study population consists of patients who had claims between 2016 and 2024 for antiretroviral (ARV) medications approved by the Food and Drug Administration (FDA) for PrEP. Data on PrEP use are available from all 50 states, Washington, DC, and Puerto Rico. Objective 1 will use descriptive and exploratory assessments to contextualize PrEP scale-up. Objective 2 will compare trends in jurisdictions implementing a particular program versus a control group of jurisdictions not implementing that program. Selection of control jurisdictions will vary depending on the level of analysis: for instance, state-level analyses may include all states, whereas analyses at the county level may include counties that are matched by relevant characteristics such as HIV prevalence or county size. Data will be analyzed retrospectively from January 1, 2016, to December 31, 2024, and we will incorporate 4 future annual data updates for the years 2025 to 2028. This study period was selected because the PrEP dataset was considered by the data provider to be internally consistent in the way it was received from pharmacies over the time period, and allows for sufficient time before the launch of EHE programs in 2019. Objective 3 will model program effects for all EHE jurisdictions on future PrEP use based on an up to 20-year time horizon, expanding our team’s existing models for 6 EHE jurisdictions [18,19].

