
#### Power Calculation: Objective 2

The study design achieves 90% power to detect a minimum difference between intervention and control county PrEP rate means of 2.4 PrEP starts per 100,000 population. This is based on a sample size of 8,784,000 county-person-month observations, a figure obtained from a minimum estimate of 6 counties implementing a particular program and 238 control counties not implementing the program. We assume that each county has an average of 300 individual PrEP users (a conservative estimate because the 2021 average and median county PrEP users are 1210 and 482), and we assume an average of 60 months of follow-up (a conservative estimate because the total follow-up period is 144 months). The standard deviation of PrEP use at the county level is 73, and we conservatively assumed a small (0.05) within-person correlation. The power assessment is based on a time-by-treatment interaction test using a mixed-model analysis with a significance of 0.05. We performed a similar analysis for state-level policies and found a minimum detectable difference of <3 additional PrEP starts. Power calculations were performed in PASS 2022.

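### The Objective 2 power statement prints 8,784,000 observations, exactly twice the product of its own inputs, and its 144-month follow-up matches neither data window in the protocol

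*Protocol article*

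**What the plan says.** The section Power Calculation: Objective 2 claims 90% power to detect a difference of 2.4 PrEP starts per 100,000 population between intervention and control counties. On sample size it says: "This is based on a sample size of 8,784,000 county-person-month observations". It traces that total to "a minimum estimate of 6 counties implementing a particular program and 238 control counties not implementing the program". It then adds "We assume that each county has an average of 300 individual PrEP users" and "we assume an average of 60 months of follow-up", and describes the 60 months as "a conservative estimate because the total follow-up period is 144 months". The remaining inputs are a county-level standard deviation of 73, a within-person correlation of 0.05, a significance level of 0.05 (sidedness not stated) and a time-by-treatment interaction test in a mixed model. The software is named as PASS 2022, but the procedure within it is not.

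The data window is defined elsewhere. For the difference-in-differences analyses, Data Analyses describes control jurisdictions "using 9 years of monthly PrEP use data (2016-2024"). Research Setting and Population gives January 1, 2016 to December 31, 2024 and adds that "we will incorporate 4 future annual data updates for the years 2025 to 2028".

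**The concern.** The paragraph presents its total as derived from the inputs printed beside it, so a reader should be able to multiply them and recover it. That fails by a factor of two. A reader then cannot tell whether the total is misprinted, an input is misprinted, or a factor has been left out. It is also unclear which sample size produced the detectable difference of 2.4.

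The 144 months is a second loose figure. It is the reason given for regarding 60 months as cautious, and it corresponds to no period the protocol defines.

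The paragraph is relied on later. The Limitations section cites the power calculations as assurance that the program and policy analyses will have enough data even if EHE funding stops. That assurance should rest on figures that agree with each other.

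**Working it through.** **Inputs, all from Power Calculation: Objective 2 unless noted**
- Counties: 6 + 238 = 244
- Users per county: 300
- Average follow-up: 60 months
- Printed total: 8,784,000
- Printed total follow-up: 144 months
- SD 73, correlation 0.05, power 90%, alpha 0.05 (two-sided is assumed here)
- Data windows (Research Setting and Population; Data Analyses): 2016-2024, and 2016-2028 with the four updates

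**Step 1. Reproduce the total.**
244 × 300 × 60 = 4,392,000, and 8,784,000 / 4,392,000 = 2.000. The plan's figure is not reproduced, and the gap is an exact doubling, so rounding does not explain it.

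**Step 2. What would give the printed total?**
- Months: 8,784,000 / (244 × 300) = 120
- Users per county: 8,784,000 / (244 × 60) = 600
- Counties: 8,784,000 / (300 × 60) = 488

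None of these is stated as an input. Other figures in the protocol do not give it either:

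| Variant | Product |
|---|---|
| 238 control counties only, 300 users, 60 months | 4,284,000 |
| 244 counties, 300 users, 108 months | 7,905,600 |
| 244 counties, 300 users, 144 months | 10,540,800 |
| 244 counties, 300 users, 156 months | 11,419,200 |
| 244 counties, 482 users (2021 median), 60 months | 7,056,480 |
| 244 counties, 1210 users (2021 average), 60 months | 17,714,400 |

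**Step 3. Follow-up.**
- 2016-2024: 9 × 12 = 108 months
- 2016-2028: 13 × 12 = 156 months
- 144 / 12 = 12 years, a span the protocol does not define

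So 144 is 36 months above the first window and 12 months below the second. Sixty months is below both.

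**Step 4. Which size goes with 2.4?**
The procedure is not given, so this step uses an assumed formula: a difference in linear slopes (time by treatment), expressed as the difference accumulated by the end of follow-up.

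Variance = SD² × (1 − ρ) × 12(t − 1) / [t(t + 1)] × (1/n₁ + 1/n₂)

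Detectable difference = (1.960 + 1.282) × √variance

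*Stated inputs.* n₁ = 6 × 300 = 1,800; n₂ = 238 × 300 = 71,400; t = 60.
- 12 × 59 / (60 × 61) = 0.1934
- 1/1,800 + 1/71,400 = 0.0005696
- Variance = 5,329 × 0.95 × 0.1934 × 0.0005696 ≈ 0.558, square root ≈ 0.747
- Detectable difference ≈ 3.2415 × 0.747 ≈ 2.42 (power at 2.4 is 89.5%)

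*Months doubled (t = 120).* The time factor becomes 12 × 119 / (120 × 121) = 0.0983, and the detectable difference is about 1.73.

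*Users or counties doubled.* 2.42 / √2 ≈ 1.71.

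**Step 5. Sensitivity to the assumed formula, on the stated inputs.**
- Difference in means over follow-up, variance inflated by 1 + 59 × 0.05 = 3.95: about 1.45
- Pre/post contrast splitting the 60 months, variance factor 4 × 0.95: about 1.42

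The match to 2.4 therefore depends on the slope formula.

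**The case against.** The strongest reply is that nothing in the design depends on the printed total. The study uses existing claims data, and 8,784,000 sets no recruitment target, allocation or stopping rule. If 2.4 was computed from the itemised inputs, the error is confined to one printed number and the power conclusion is unchanged. The 144 months does not enter the product or the detectable difference either, and 60 months is below both real windows. All of this stands, and it limits the point to a correction of the text plus a confirmation.

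A second reply is that the factor of 2 might be real but unwritten, for example 60 months before and 60 after implementation. That would give 120 months and the printed total. The protocol does not say so. A full 120 months per county also would not fit in the 108 months of 2016-2024 data, and under the slope approximation it would give about 1.73 rather than 2.4.

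Three stronger readings are tempting, and the document does not support them.
- A reader might infer that the stated size and 2.4 are proven incompatible. They conflict under one assumed formula. The paragraph itself speaks of a difference between rate means, and other formulas give other values. For instance, a pre/post contrast over 120 months with a fourfold variance inflated by 1 + 119 × 0.05 gives about 2.45 one-sided and 2.72 two-sided. That is a less natural form for an interaction test, but it shows the check is suggestive only.
- A reader might infer that follow-up is overstated by a third. That holds against 108 months; against 156 months, 144 is too short. The direction of the error is not established.
- A reader might infer that all of Objective 2's power is undermined. The section also reports a state-level calculation with a detectable difference below 3, and this discrepancy does not touch it.

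**Conclusion.** The power paragraph is wrong as printed in two places. The total of 8,784,000 is exactly twice the 4,392,000 that its own inputs give; this is plain arithmetic and needs no assumption. The 144-month follow-up agrees with neither the 108-month nor the 156-month window, and nothing else in the article reconciles it.

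The consequence for the detectable difference is less certain. With a two-sided 0.05 test, SD 73, correlation 0.05 and the slope-difference approximation, the undoubled inputs give about 2.42 and the doubled size about 1.7. The likelier explanation is that 2.4 was run on 4,392,000 and the total was misreported. Without the PASS procedure and settings this cannot be settled from the document. The description of 60 months as a cautious choice survives. It is a correction worth making because the Limitations section relies on this calculation; it is not evidence that the study lacks power.

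**What to change.** In Power Calculation: Objective 2:
1. Restate the total as 4,392,000, or state and justify the missing factor of 2 and show which input carries it.
2. Replace 144 months with 108 if 2016-2024 is meant, or 156 if the 2025-2028 updates are included, and name the window.
3. Rerun the calculation once on that single set of inputs, confirm or replace 2.4, and name the PASS procedure and the sidedness of the test.

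The cost is a few words of text and one rerun of the power software. No data collection or analysis changes.

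### The 90% power for 2.4 PrEP starts per 100,000 is not supported: 300 PrEP users per county are counted as replicates of a county rate, with no county-level variance

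*Protocol article*

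**What the plan says.** Under Power Calculation: Objective 2 (Protocol article), the design "achieves 90% power to detect a minimum difference between intervention and control county PrEP rate means of 2.4 PrEP starts per 100,000 population". The sample is described so: "This is based on a sample size of 8,784,000 county-person-month observations", obtained from "a minimum estimate of 6 counties implementing a particular program and 238 control counties not implementing the program". On cluster size: "We assume that each county has an average of 300 individual PrEP users". Follow-up is taken as 60 months. The variance inputs are: "The standard deviation of PrEP use at the county level is 73, and we conservatively assumed a small (0.05) within-person correlation". The test is a time-by-treatment interaction in a mixed model at significance 0.05. A similar calculation for state policies is reported with a detectable difference below 3 starts, without its inputs.

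Under Data Analyses, the unit is fixed: "Health jurisdictions implementing a program or policy will be the primary intervention unit". Under Primary Outcome Measures, PrEP starts are a count of persons per 100,000 population, so the outcome is an aggregate rate. The Limitations section relies on the result if Ending the HIV Epidemic (EHE) funding stops: "based on our power calculations, we still will have sufficient data to perform the program and policy analyses".

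**The concern.** A starts-per-100,000 rate has one value per county and month. The 300 PrEP users in a county are not 300 independent measurements of it, and more users cannot reduce the variation between counties in how their rates change. With 6 program counties, that variation limits precision, and the stated inputs contain no term for it: the only correlation is within person.

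The SD is also misplaced twice. It is described as a county-level figure, but the result follows only if it is used as a person-level one. It describes PrEP use, while the target difference is in PrEP starts.

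The calculation sets no enrolment, so the consequence lies in interpretation. Readers will judge null program results against a published 90% power, the modeling under Objective 3 takes forward the programs found effective, and the reassurance about lost funding rests on this figure.

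**Working it through.** **Inputs from the power section:** 6 and 238 counties; m = 300 users per county; T = 60 months; SD = 73; correlation ρ = 0.05; significance 0.05; power 90%. Assumptions: two-sided test (sidedness is not stated), normal approximation, so the multiplier is 1.960 + 1.2816 = 3.2415.

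**1. Reproducing 2.4.** For a slope-difference test with no county-specific slopes, the standard error of the difference in change over follow-up is

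SE = (T − 1) × √[ SD²(1 − ρ)/Sxx × (1/(6m) + 1/(238m)) ], with Sxx = T(T² − 1)/12 = 60 × 3599/12 = 17,995.

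Here 73² × 0.95/17,995 = 0.2813, and 1/6 + 1/238 = 0.17087. With m = 300, SE = 59 × √(0.2813 × 0.17087/300) = 0.747. The detectable difference is 3.2415 × 0.747 = **2.42**, and power at 2.4 is 89.5%. Of the variants tried (contrast of means over time, half-pre/half-post contrast, design effects, 60/120/144 months, 300/600 users, ρ of 0 or 0.05), only this one matches. It implies a county-month SD of 73/√300 = 4.2, not 73.

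**2. The observation count.** 244 × 300 × 60 = 4,392,000, exactly half of 8,784,000. The larger total needs 600 users or 120 months; either gives a detectable difference of about 1.7 and over 99% power. The 2.4 therefore belongs to the smaller count.

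**3. County as the unit.** Setting m = 1 gives SE = 59 × √(0.2813 × 0.17087) = 12.94 and a detectable difference of **41.9**, which is √300 = 17.3 times larger. Power at 2.4 is about 5%. For a contrast of 30 months before with 30 after, SE = √[73²(1 − ρ) × 4/60 × 0.17087], giving 24.6 at ρ = 0.05. In both, ρ is now a within-county month-to-month correlation, which the article does not give, so a range is assumed:

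| Assumed ρ | Slope: detectable difference | Slope: power at 2.4 | Half-pre/half-post: detectable difference | Half-pre/half-post: power at 2.4 |
|---|---|---|---|---|
| 0.05 | 41.9 | 5% | 24.6 | 6% |
| 0.5 | 30.4 | 6% | 17.9 | 7% |
| 0.9 | 13.6 | 9% | 8.0 | 16% |
| 0.95 | 9.6 | 13% | 5.6 | 28% |
| 0.99 | 4.3 | 44% | 2.5 | 87% |

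Detecting 2.4 with 90% power needs ρ of about 0.997 (slope) or 0.991 (half-pre/half-post), with no county-specific trends.

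**4. Keeping the 300 users but letting counties differ in trend.** With τ the between-county SD of change per 100,000 over follow-up (assumed), SE = √[0.747² + τ² × 0.17087].

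- τ = 2: SE = 1.114, detectable difference 3.6, power 58%.
- τ = 5: SE = 2.198, detectable difference 7.1, power 19%.

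**5. Limit set by the number of counties.** Whatever the number of users, the detectable difference is at least 3.2415 × √0.17087 = 1.34 times the SD of county-level change. So 2.4 requires that SD to be at most 2.4/1.34 = 1.8 per 100,000.

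**The case against.** The strongest reply is that difference-in-differences removes stable differences between counties, so carrying SD 73 and a correlation of 0.05 over to county rates is too harsh. That stands. The 0.05 was given for persons, and for a slope test a low within-person correlation is indeed the cautious choice; the fault is the missing county component. The 41.9 is the unfavourable end of a range, not an estimate.

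The SD of 73 also describes PrEP use. As a scale check, 1,079,942 patients over 108 months is about 10,000 first starts a month, or about 3.0 per 100,000 with an assumed population of 330 million. If the rate is monthly, which the article does not say, 41.9 is about 14 times that mean, while the required SD of change, 1.8, is about 60% of it and not plainly out of reach.

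Six program counties is stated as a minimum. With 25 of 244, the multiplier is 3.2415 × √(1/25 + 1/219) = 0.68 and the tolerable SD of change is 3.5.

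A reader might therefore infer that the study is underpowered. The article does not support that: the within-county correlation, the trend variance and the SD of starts are all absent. Nor should one say that a current user cannot contribute a start, since reinitiation after a lapse counts. Nor does the article support a charge of inflated type I error with few treated counties. It names a mixed model for the power and the Callaway and Sant'Anna method or a similar one for analysis, and does not specify a test known to over-reject.

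None of this restores the stated figure. It shows that the answer depends on county-level quantities that the calculation left out.

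**Conclusion.** The concern holds as a fault in the stated basis. The 90% power for 2.4 per 100,000 arises only when PrEP users are treated as independent replicates of a county rate, with a county-level SD of use standing in for a person-level SD of starts. It does not follow from a design that assigns programs to jurisdictions.

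On the article's SD of 73, 6 against 238 counties and 60 months, the detectable difference lies between 41.9 and 4.3 (slope) or 24.6 and 2.5 (half-pre/half-post) for assumed within-county correlations from 0.05 to 0.99. Those figures assume no county-specific trends and a normal approximation, which is favourable with 6 treated counties. The article itself treats parallel trends as something to be tested, so zero trend variance cannot be taken as given.

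Actual power remains unknown. The twofold error in the observation count is certain arithmetic. The state-level figure is described as coming from a similar analysis, so it needs the same check, but it cannot be recomputed from what is shown.

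**What to change.** - Recompute power on the county-month panel for the planned difference-in-differences, using the between-county SD of change in PrEP starts per 100,000 estimated from the 2016-2024 data already held. Show 6 treated counties as the minimum case and larger numbers beside it.
- Repeat this on the state-month panel, and state the inputs.
- State the period of the rate, the within-county correlation and the trend variance used.
- Correct the observation count so that it equals the product of its factors.
- Restate both detectable differences (2.4 and below 3), and revise the Limitations sentence on discontinued funding to match.

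The cost is a little analysis work on data in hand and, very probably, a less favourable stated figure. No new data collection is needed.
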